### Sample size estimation

2.5

Whitehead et al. suggested that the estimated sample size of randomized controlled pilot trials with 90% power and 2-tailed 5% significance should be 75, 25, 15, and 10 for each treatment arm with the standardized effect sizes of extra small (0.1), small (0.2), medium (0.5), or large (0.8), respectively (25, 32). The primary outcome eGFR slope is used to estimate the sample size in our pilot trial. The exact effect size is calculated by the minimum clinically important difference (MCID) of the eGFR slope and the mean value of the control group. The mean value of 3.79 of the placebo-control group in the DAPA-CKD trial (13) is selected for the estimation. The MCID of the eGFR slope is 0.75 mL/min/1.73m^2^ based on the evidence from randomized controlled trials and observational studies with large enough sample sizes (33, 34). Given that a change in 0.75 is the MCID from the mean value of 3.79, a 20% difference would be clinically significant. The 20% change (0.2) is used as our effect size. Thus, we will recruit 25 participants for each treatment arm accordingly. With an approximate 15% attrition rate based on our previous clinical study (23), we plan to recruit 60 participants, with 30 participants for each arm in this study.

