#### Efficacy outcomes

2.9.2

The efficacy of TQF for people with stage 2-4 DKD will be assessed on renal-related outcomes every 12 weeks.

The eGFR slope will be measured at the end of the treatment. eGFR slope is a validated surrogate endpoint for clinical trials to indicate kidney disease progression (33, 34). The Chronic Kidney Disease Epidemiology Collaboration (CKD-EPI) equation will be used to calculate eGFR (36).

Other efficacy outcomes will be measured from baseline to the end of treatment: changes in UACR, UPCR, serum creatinine, blood urea nitrogen, uric acid, HbA1c, fasting blood glucose (FBG), and blood lipids (cholesterol, triglycerides, low-density lipoprotein cholesterol, and high-density lipoprotein cholesterol). The laboratory equipment for all the laboratory outcomes will be standardized and follow a consistent operating procedure. Additionally, the changes in the score of the Dampness Syndrome Scale of Chinese medicine and the survival time of renal composite endpoint events will also be evaluated (35). The survival time is defined as starting from baseline to the occurrence of any of the below composite endpoints (37): receipt of a kidney transplant, initiation of maintenance dialysis, death from kidney failure, a sustained low eGFR, and a sustained percent decline in eGFR.

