### Statistical analysis

2.14

The quantitative data will be processed and analyzed by an independent statistician at GPHCM using PASW 18.0 (IBM SPSS Inc., Armonk, New York, USA) and Stata (Version 15.0, Stata Corp. College Station, TX, USA) with two-tailed 5% significance.

We will perform the primary analysis on the full analysis population following the Intent-to-Treat (ITT) principle. The full analysis population refers to randomized participants who received at least one dose of treatment and had baseline data along with at least one post-baseline efficacy assessment. We will also conduct a per-protocol analysis as a secondary analysis, including participants who completed the study without significant protocol violations. Safety analysis will be performed on the randomized participants who have received at least one dose of TQF or placebo.

Descriptive analysis will be performed on demographic and baseline characteristics. Categorical variables will be summarized as frequencies and percentages. The difference between the two groups will be assessed with a *chi*-squared test. Continuous variables will be reported as means with standard deviations for or medians with interquartile ranges. The difference between the two groups will be detected by Student’s *t*-test for normally distributed data, or the Mann-Whitney U-test for non-normally distributed variables.

The primary efficacy outcome eGFR slope will be assessed through a linear mixed-effects model in which treatment and the interaction of treatment and time are treated as a fixed effect while the time effect is a random effect using an unstructured covariance matrix. A secondary analysis for the eGFR slope will be conducted through the superiority test with a 95% confidence interval (CI), to explore any clinical disparities associated with TQF.

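### The eGFR-slope mixed model in section 2.14 states no fixed effect of time, so with 0/1 treatment coding its interaction term estimates the TQF arm's own slope and not the difference from placebo

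*Protocol article*

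**What the plan says.** Section 2.14 (Statistical analysis) calls eGFR slope the primary efficacy outcome and plans a mixed model for it. Of the model's terms it says: "treatment and the interaction of treatment and time are treated as a fixed effect while the time effect is a random effect". The covariance is to be unstructured. Testing is "with two-tailed 5% significance". The section does not say how treatment is coded, or which coefficient or contrast is to be reported as the slope difference. It adds a superiority test with a 95% confidence interval as a secondary analysis of the slope, without saying how the slope in that test is obtained.

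Section 2.5 (Sample size estimation) plans on a control arm that declines: "The mean value of 3.79 of the placebo-control group in the DAPA-CKD trial (13) is selected for the estimation". It continues: "Given that a change in 0.75 is the MCID from the mean value of 3.79, a 20% difference would be clinically significant". Section 2.9.2 (Efficacy outcomes) adds: "The eGFR slope will be measured at the end of the treatment".

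**The concern.** The sentence in section 2.14 divides the terms into two lists. Treatment and treatment-by-time are fixed, and time is random. A random effect describes how participants vary around a mean of zero, so it cannot represent an average fall in eGFR. Read literally, the model gives the reference arm a mean slope of zero. Section 2.5 assumes a control slope of 3.79, so the model conflicts with the trial's own planning figure.

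Two things are at stake. The first is the estimate: under one common coding, the coefficient that a reader would take as the treatment effect answers a different question, namely whether eGFR falls on TQF. The second is the variance. The Discussion says the pilot should help estimate the effect size and power the full-scale trial, and a decline that has no fixed term is absorbed into the random-slope variance.

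**Working it through.** **Inputs from the article.** Control mean slope 3.79 and minimum important difference 0.75 (section 2.5); 30 per arm (section 2.5); five eGFR values over 48 treatment weeks (Table 1); two-sided 5% (section 2.14).

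**Assumptions.** The 3.79 is a decline in mL/min/1.73m² per year. The article gives no slope SD for this trial. Its only spread is the 2.58 beside the single-arm result in the Introduction, taken here as an SD. The SD of a participant's observed slope, s, is therefore varied from 2.58 to 12.

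**The plan's own figures.** 0.75/3.79 = 0.198, the stated 20%. 25/(1 - 0.15) = 29.4, rounded up to 30 per arm and 60 in total. Both reproduce, and neither depends on the mixed model.

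**Literal model, treatment coded 0/1 (TQF = 1).** Write the mean as b0 + b1·treatment + b2·treatment·time. In the placebo arm the mean slope is fixed at 0. In the TQF arm it is b2. With complete balanced data the estimate of b2 is the TQF arm's mean slope.

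- Both arms truly at -3.79: b2 averages -3.79. The true difference is 0.
- True benefit of 0.75: b2 averages -3.79 + 0.75 = -3.04. The sign is reversed.

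The placebo arm's departure from zero enters the pooled slope variance. With m_c the control mean slope, the model-based SE² = (s² + m_c²/2)/n, and m_c²/2 = 3.79²/2 = 7.18. The true sampling SD of the estimate is s/√n.

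For s = 6, n = 30: SE = √((36 + 7.18)/30) = 1.20. Significance needs an estimate below -1.96 × 1.20 = -2.35. The sampling SD is 6/√30 = 1.095. The chance is Φ((3.79 - 2.35)/1.095) = Φ(1.31), about 90%.

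Results from 40,000 simulated trials per setting, 30 per arm:

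| s | model SE | significant harm, no effect | significant harm, true benefit 0.75 | 2-df test rejects, no effect |
|---|---|---|---|---|
| 2.58 | 0.68 | 100% | 100% | 100% |
| 6 | 1.20 | 90% | 74% | 99% |
| 8 | 1.54 | 70% | 51% | 90% |
| 10 | 1.89 | 52% | 37% | 73% |
| 12 | 2.24 | 40% | 27% | 56% |

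With 25 per arm the no-effect harm rates are 100%, 84%, 62%, 45% and 34%. If both arms decline by only 2.61 (30 per arm), they are 99.9% at s = 2.58, 63% at 6 and 41% at 8.

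**Fitted mixed models.** In 500 simulated trials with random-slope SD 3 and residual SD 4 (observed-slope SD about 6.2), the literal 0/1 model averaged -3.82 and was significant in 88%. The model with fixed time averaged 0.03 and was significant in 5.6%. A second check of 80 trials at s = 3.77 gave a mean of -3.76, significant in all. Some fits in that check gave convergence warnings, so it supports the algebra more than any exact rate.

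**Other codings.** With treatment as a factor and no time main effect, the interaction holds one slope per arm. This is the corrected model in another parameterisation: the contrast of arm slopes equalled the corrected interaction (0.3068 in both fits). The default 2-df test instead asks whether both slopes are zero (last column). With -1/+1 coding, the coefficient averaged -0.04 under no effect, with no harm signal in 80 trials.

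**With fixed time added.** Under no effect the interaction averages about 0 and is significant in about 5% of trials. A true benefit of 0.75 is estimated as about 0.75.

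**The case against.** The best defence is that the sentence is condensed wording for a random slope added to an ordinary fixed time trend. An unstructured covariance suggests a random intercept and slope, and a team that plans on a control slope of 3.79 is unlikely to intend a mean of zero. This is a journal article, and coding and contrasts normally sit in the analysis plan. That may well describe the intention. But the article chose to list the fixed and random terms for this outcome, and the list leaves out one that the model needs.

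A reader might infer that the model cannot estimate the slope difference at all, or that it would report harm whatever the analyst does. The article does not support that. It states no coding. Factor coding, available in both named packages, gives a valid contrast with the correct variance, and -1/+1 coding removes the false signal. Even with 0/1 coding, the harm rate falls to about 40% at an SD of 12.

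A reader might also infer a conflict over the time window, because Table 1 marks eGFR slope at week 62, off treatment. The same row marks baseline, where no slope exists, so it is a measurement schedule. Section 2.9.2 ties the slope to the end of treatment.

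Two further points limit the stakes. Feasibility is the primary outcome of this pilot (section 2.9.1), and a separate superiority test of the slope is planned. That test is a safeguard only if its slope does not come from the same coefficient, which the article does not say.

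**Conclusion.** The model is wrong as written, and the consequence depends on an unstated coding. With 0/1 coding the interaction is centred on -3.79 under no effect and on -3.04 under the benefit the trial regards as important. The displacement needs only the planned decline of 3.79 per year. The false-harm rate also needs a slope SD: about 100% at 2.58, 90% at 6, 52% at 10 and 40% at 12, with 30 per arm.

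With factor coding the slope contrast is sound and the variance estimates are those of the corrected model, but the default interaction test does not test the treatment effect. With 0/1 coding, the extra 7.18 in the slope variance would also distort full-scale planning. Against an assumed between-participant slope variance of 9 (SD 3), it is an inflation of 7.18/9, about 80%. The sample size of 60 is unaffected.

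**What to change.** Restate the model in section 2.14: fixed effects of treatment, continuous time and treatment-by-time; a random intercept and a random slope for each participant, with an unstructured 2×2 covariance. Name the treatment-by-time coefficient (equivalently, the contrast of the two arm slopes) with its 95% confidence interval as the treatment effect.

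As a minor clarification, say that the primary slope uses the on-treatment visits t1 to t5, in line with section 2.9.2. Estimation by REML, a small-sample degrees-of-freedom correction and a centre term are optional and can be left to the analysis plan.

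The cost is one or two sentences. No extra data, visits or participants are needed.

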### Randomization

2.6

After a two-week run-in period, participants who meet the inclusion criteria will be randomly assigned to either the TQF group or the TQF placebo group at a 1:1 ratio. The personnel from the Key Unit of Methodology in Clinical Research (KUMCR) at GPHCM conducted the randomization. SAS 9.3 (SAS Institute, Cary, NC, USA) software will generate random allocation sequences by stratified block methods. To ensure allocation concealment, the randomization numbers are delivered to study sites via a validated web-based randomization system, Interactive Web Response System for Chinese Medicine Trials. Every participant will be assigned a random number, and a comprehensive record of all procedures will be documented and preserved.

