The secondary outcome time to composite renal endpoint events will be analyzed by the Kaplan-Meier method. The log-rank test will be employed to compare time to composite outcomes between the two groups, followed by Cox proportional hazards regression to estimate hazard ratios with 95% CIs. Other continuous outcomes will be performed by Student’s *t*-test or Mann-Whitney U-test, while categorical variables will be examined using the *chi*-square test or Mann-Whitney U-test. The Cochran-Mantel-Haenszel test will be used for categorical variables, adjusting for center-related effects. Subgroup analysis will consider risk factors including but not limited to age, gender, hypertension, and proteinuria. Additionally, the Fisher exact test will be utilized to compare the incidence rates of adverse events and adverse drug reactions throughout the treatment duration.

An ITT analysis will be applied using the imputation method for missing data. We expect less than 20% of missing data points. The linear trend at point method will be used to replace missing values. The existing series will be regressed on an index variable scaled from 1 to n, and the missing values will be replaced with their predicted values. If the predicted values cannot be computed, the last observation carried forward (LOCF) method will be used. We will perform a sensitivity analysis without imputation to assess the robustness of our results.

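### Continuous secondary outcomes are compared as unadjusted changes from baseline: a valid test, but less precise than a baseline-adjusted analysis of data already collected

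*Protocol article*

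**What the plan says.** All references are to the protocol article.

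- **Test.** Statistical analysis (2.14): "Other continuous outcomes will be performed by" Student's t-test or the Mann-Whitney U-test. No covariate is named.
- **Form of the outcomes.** Efficacy outcomes (2.9.2): "Other efficacy outcomes will be measured from baseline to the end of treatment: changes in UACR, UPCR, serum creatinine", followed by blood urea nitrogen, uric acid, HbA1c, fasting glucose and four lipids. The change in the dampness score is added in the same section, which makes 12 measures.
- **Baseline data.** The full analysis population must have "had baseline data along with at least one post-baseline efficacy assessment". Table 1 schedules the laboratory measures at the allocation visit and every 12 weeks after it.
- **Center.** "The Cochran-Mantel-Haenszel test will be used for categorical variables, adjusting for center-related effects". No matching statement is made for the continuous two-sample tests.
- **Randomization (2.6).** SAS "will generate random allocation sequences by stratified block methods". The stratification factors are not named.
- **eGFR slope.** This outcome "will be assessed through a linear mixed-effects model in which treatment and the interaction of treatment and time are treated as a fixed effect". It is therefore outside this point.

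**The concern.** Subtracting the baseline uses it only in part. A change score in effect fixes the slope on baseline at 1, whereas the best slope, when the two standard deviations are equal, is the correlation between baseline and end of treatment. Unless that correlation is 1, the comparison carries avoidable noise. A chance difference between arms at baseline also leaks into the observed difference in change: the arm that starts higher tends to fall more.

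The stake is the precision of the secondary efficacy estimates in a trial of 60. The Discussion says that the pilot is to help estimate the effect size for a full-scale trial, so these estimates may be used again. Center is treated as worth adjusting for in one type of outcome but not in the other, with no reason given.

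**Working it through.** **The plan's own size.** Sample size estimation (2.5) takes 25 per arm and about 15% attrition: 25/0.85 = 29.4, rounded up to 30 per arm, 60 in total. This reproduces. The 25 is looked up from a pilot-size rule, so the choice of test below does not alter it.

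**Variance.** Let sigma be the common standard deviation at baseline and at end of treatment, and rho their correlation. The documents give no rho, so a range is assumed.

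- Change score: 2·sigma²·(1−rho).
- ANCOVA on baseline: sigma²·(1−rho²).
- Ratio: (1−rho)(1+rho) / [2(1−rho)] = (1+rho)/2.

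| Assumed rho | Ratio | Reduction | 60 under ANCOVA match, under change score |
|---|---|---|---|
| 0.5 | 0.75 | 25% | 60/0.75 = 80 |
| 0.7 | 0.85 | 15% | 60/0.85 = 71 |
| 0.8 | 0.90 | 10% | 60/0.90 = 67 |
| 0.9 | 0.95 | 5% | 60/0.95 = 63 |

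Estimating the baseline slope costs a little in a small sample. The factor is about 1 + 1/(2n−4) = 1 + 1/56 at n = 30 per arm, which moves the ratios at rho 0.5, 0.7 and 0.9 to 0.763, 0.865 and 0.967.

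**Power.** The true difference is assumed to be 0.5 baseline SD, with 30 per arm and two-sided 5% (normal approximation):

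| Assumed rho | t-test on change | ANCOVA |
|---|---|---|
| 0.5 | 49.1% | 60.9% |
| 0.7 | 70.5% | 77.4% |
| 0.9 | 99.1% | 99.3% |

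A simulation with 5,000 runs per setting, its ANCOVA also including a two-level center, gave 48.5% against 59.4% at rho 0.5 and 69.4% against 75.4% at rho 0.7.

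**Center, as illustration only.** With an assumed center effect of 0.5 SD, the unadjusted change test fell to 45.0% (rho 0.5) and 67.0% (rho 0.7). ANCOVA with center gave 58.1% and 75.1%. With no treatment effect and rho 0.3, 0.5 and 0.7, the unadjusted change test rejected in 4.3% to 4.7% of runs and ANCOVA in 4.9% to 5.5%.

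**Chance imbalance.** With 30 per arm the standard error of a baseline difference is sqrt(2/30) = 0.258 SD. A difference of at least 0.25 SD in either direction corresponds to |Z| ≥ 0.25/0.258 = 0.97, a probability of about 33% per measure. Over 12 measures about four are expected. Given an imbalance of 0.25 SD, the change score is displaced by (1−rho)·0.25: 0.125, 0.075 and 0.025 SD at rho 0.5, 0.7 and 0.9. ANCOVA removes this.

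**The case against.** The strongest reply is that this is a preference about efficiency and not an error. A two-sample test on change is valid under randomization, and the simulated rejection rates bear that out. The displacement from imbalance is conditional on the imbalance seen and averages to zero over randomizations. Feasibility is the primary outcome, and the efficacy outcome used for sizing has its own longitudinal model. The gain depends wholly on an assumed correlation and is only 5–10% at 0.8–0.9. The formula also assumes equal standard deviations and a t-test, so it does not size any loss for skewed measures under Mann-Whitney. All of this stands, and it limits the weight of the point. It does not remove the point, because the article names the test: ANCOVA would replace a stated method, not supply a detail left to an analysis plan.

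Four stronger readings are tempting, and the documents do not support them.

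- **A far larger gain, 1−rho².** That ratio applies to a t-test on end-of-treatment values. The plan tests changes.
- **Skewed markers will have only a p-value and no usable estimate.** The article nowhere says that only p-values will be reported. It mentions means with standard deviations, or medians with interquartile ranges, for continuous variables, although in the paragraph on baseline description.
- **The analysis ignores the randomization strata.** The strata are not named. Center is a reasonable guess from the two-site design and the Cochran-Mantel-Haenszel sentence, but no more.
- **The eGFR model wrongly omits center.** An article need not list every covariate of a mixed model.

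**Conclusion.** The point holds as a modest, worthwhile improvement to the secondary efficacy analysis. The stated tests are valid but less precise than a baseline-adjusted analysis. The variance falls by 25%, 15% or 5% at assumed correlations of 0.5, 0.7 or 0.9, slightly less after the small-sample cost, and chance baseline imbalance no longer affects the estimates. The figures rest on equal standard deviations and on correlations that the documents do not give. The part of the gain due to center or other strata cannot be sized from the article. Neither the primary feasibility outcome nor the eGFR-slope model is affected.

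**What to change.** Replace the two-sample tests for these outcomes with ANCOVA, or with a repeated-measures mixed model on the 12-weekly values. Include arm, baseline value and center, plus any other factor actually used to stratify. Analyze skewed measures such as UACR and UPCR on the log scale. Report the adjusted difference, or the geometric mean ratio for logged measures, with its 95% confidence interval. Keep Mann-Whitney as a sensitivity check.

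The trial is registered and under way, so the change should be a documented amendment made before unblinding. That is the whole cost: no added patients, visits or assays. One check is needed: the Table 1 row for the dampness score shows no visit marks in the text at hand, perhaps through extraction, so the timing of its baseline assessment should be confirmed.

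### The primary eGFR slope analysis rests on single linear-trend imputation that the planned mixed model does not need and that can cost precision, from negligibly to more than double the variance

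*Protocol article*

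**What the plan says.** All of the relevant text is in the protocol article, Statistical analysis.

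- Population: "We will perform the primary analysis on the full analysis population following the Intent-to-Treat (ITT) principle". Members must have been randomised and dosed, and must have "had baseline data along with at least one post-baseline efficacy assessment".
- Model: "The primary efficacy outcome eGFR slope will be assessed through a linear mixed-effects model", with a random time effect and unstructured covariance.
- Missing data: "An ITT analysis will be applied using the imputation method for missing data". The method is then named: "The linear trend at point method will be used to replace missing values". It works as follows: "The existing series will be regressed on an index variable scaled from 1 to n", and predictions from that regression fill the gaps. LOCF applies only where no prediction can be computed. Fewer than 20% of data points are expected to be missing.
- Observed data only: "We will perform a sensitivity analysis without imputation to assess the robustness of our results".

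Sample size estimation gives about 15% attrition and 30 participants per arm. The Abstract and Table 1 give 12-weekly assessments over 48 weeks of treatment.

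**The concern.** A likelihood-based mixed model does not need complete rows. Under missing at random it uses each participant's observed visits and gives short records less weight in the slope. Filling the gaps first removes that weighting. A participant seen only at baseline and week 12 gets a line through two noisy values, extended to week 48, and then counts as much as someone measured five times.

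The rule also does not say what the series is. If it is the participant's own visits, the result is the extrapolation just described. If it is a visit's column of values indexed by case number, the filled value depends on position in the file and ignores the participant's own eGFR and arm.

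The eGFR slope is the primary efficacy outcome, and the Discussion says the pilot should help estimate the effect size for a full-scale trial. The precision of the slope difference and the variance components behind it are what that later trial would use.

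**Working it through.** **Plan's own figure.** 0.75/3.79 = 0.198, taken as 0.2; the rule of thumb then gives 25 per arm; 25/0.85 = 29.4, so 30 per arm and 60 in total. This reproduces. The plan states no figure for the effect of imputation.

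**Inputs from the article.** 30 per arm; on-treatment visits at weeks 0, 12, 24, 36 and 48; about 15% attrition; under 20% of data points missing; at least one post-baseline assessment.

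**Assumed, because the article does not give them.** Slope SD s, residual SD e, the timing of dropout, random intercept and slope, and variances known to the observed-data model (which slightly favours it). The worked case uses s = 3 per year and e = 4; ranges follow.

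**Step 1: one participant's slope.** With k visits, v(k) = s² + e²/Sxx(k), where Sxx is the sum of squared deviations of visit times in years. Visit spacing is 12/52.18 = 0.230 years and its square is 0.0529. Sxx is 0.5, 2, 5 and 10 times this for k = 2, 3, 4 and 5: 0.0264, 0.1058, 0.2644 and 0.5289. So v = 614.1, 160.3, 69.5 and 39.3.

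**Step 2: two ways of combining.** Points filled in on a participant's own fitted line leave that participant's slope unchanged. The data then look balanced, so the arm slope is the unweighted mean of individual slopes and its variance depends on the arithmetic mean of v. The observed-data mixed model weights by precision, so its variance is very nearly the harmonic mean of v. The variance ratio is arithmetic mean over harmonic mean.

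For 15% dropout, one third each last seen at weeks 12, 24 and 36:
- imputed: 0.85×39.25 + 0.05×(614.1 + 160.3 + 69.5) = 75.6
- observed: 1/[0.85/39.25 + 0.05×(1/614.1 + 1/160.3 + 1/69.5)] = 43.9
- ratio 1.72; SE of the difference √(2×75.6/30) = 2.24 against √(2×43.9/30) = 1.71

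| Dropout pattern (s = 3, e = 4) | Imputed | Observed | Ratio |
|---|---|---|---|
| 15%, last visit week 36 | 43.8 | 42.0 | 1.04 |
| 15%, last visit week 24 or 36 | 50.6 | 43.1 | 1.17 |
| 15%, spread over weeks 12/24/36 | 75.6 | 43.9 | 1.72 |
| 15%, all after week 12 | 125.5 | 45.7 | 2.75 |
| 25%, spread | 99.8 | 47.7 | 2.09 |
| 50%, spread (20% of values missing) | 160.3 | 60.8 | 2.64 |
| 33%, all after week 12 (20% of values missing) | 230.9 | 57.1 | 4.05 |

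**Step 3: range over the SDs, within-person reading.** At 15% spread dropout the ratio is 1.35 to 1.79 for s and e each from 3 to 5, and 1.02 to 1.91 for s from 2 to 12 and e from 2 to 7. With last visits at weeks 24 or 36 it is 1.00 to 1.23. With 10 to 20% of visits missed intermittently (simulation) it is 1.00 to 1.19. With all 15% leaving after week 12 it is 1.06 to 3.22.

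**Step 4: across-case reading (simulation; s from 3 to 8, e from 3 to 5).** The ratio is about 1.5 to 3.5 at 15% spread dropout, and roughly 2 to 6 when dropout leaves 20% of values missing. With s = 4 and e = 4, a true difference of 0.75 averages 0.64 and, with 20% missing through spread dropout, 0.39.

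**Step 5: variance components a full trial would borrow (15% spread, within-person reading, s = 3, e = 4).** Filled points add no residual. A full record carries 3 residual degrees of freedom; records of 4, 3 and 2 visits carry 2, 1 and 0 but are treated as 3. The apparent residual variance is 16×(0.85×3 + 0.05×2 + 0.05×1)/3 = 14.4, SD 3.8. The apparent slope variance is 75.6 − 14.4/0.5289 = 48.4, SD about 7 against an assumed 3.

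**The case against.** Much can be said for the plan, and it narrows the point.

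- A reader might infer that the method doubles the variance or worse as a rule. It does not. At the protocol's own attrition, spread over visits, the within-person ratio stays below 2 throughout the SD range tried, and it is close to 1 for late or intermittent missingness.
- A reader might expect LOCF to bias the eGFR slope difference. LOCF is reached only when no line can be computed. Members of the analysis population have baseline data and a post-baseline efficacy assessment, and Table 1 schedules eGFR at every such visit. Two eGFR values will normally exist, so no LOCF bias figure is warranted for this outcome.
- A reader might suspect an invalid test. With data missing completely at random, simulated type I error stayed near 5% (0.02 to 0.07, 600 replicates per scenario). The harm shown is lost precision and, across cases only, dilution.
- The meaning of the series may be settled in an unseen analysis plan, so the across-case figures are conditional on that reading.
- Feasibility is the primary outcome and is untouched. The analysis without imputation is already planned. In the worked case the 95% half-width moves from 1.96×1.71 = 3.4 to 1.96×2.24 = 4.4 around a target of 0.75, which is wide either way.

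All of this stands and limits the severity. It does not supply a reason to prefer the imputed analysis: in none of the scenarios examined was it more precise than the model on observed data.

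**Conclusion.** The concern holds in a limited form. The article places a deterministic single imputation ahead of an observed-data mixed model that is valid under missing at random, and the imputation brings no information in return. The inflation of the slope-difference variance runs from negligible (about 1.0 to 1.2 times, late or intermittent missingness), through about 1.4 to 1.8 times (15% spread dropout, within-person reading, slope and residual SDs of 3 to 5), to more than double (early or heavier dropout, or the across-case reading, which also shrinks the difference). These sizes rest on assumed SDs and dropout timing. This should be fixed, but it does not threaten the trial's primary feasibility objective.

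**What to change.** Exchange the two analyses already planned. Make the linear mixed model on all observed eGFR values, without imputation and under missing at random, the primary analysis of eGFR slope, and remove linear-trend and LOCF filling from it. As sensitivity, use multiple imputation by arm with a delta-adjusted departure from missing at random, which tests the assumption the primary analysis depends on. If trend filling is kept anywhere, state whether the series is a participant's visits or a column of cases.

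The cost is a few lines of wording, best settled before unblinding, plus the programming of the multiple imputation. No new data, visits or participants are needed.
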